### Machine learning

In order to identify patient subgroups and treatment patterns, we will apply machine learning techniques, in particular variational auroencoders (VAEs) as a deep learning technique. This will allow us to cluster patients in an unsupervised manner, also taking time structure into account. This will be complemented by more standard descriptive statistics for comprehensively describing the characteristics of different patient subgroups, the disease course, and treatment paths. In years 1 and 2, this approach will primarily be used for quality control, whereby identified patterns will reveal artefacts in the data that need to be resolved, and help us prioritize measured patient characteristics for quality improvement. In year 5, the techniques will be deployed on a final analysis data set for identifying prognostically relevant patient subgroups, while also guiding propensity score development for the causal analyses described above. All analyses will be pre-specified in a statistical analysis plan.

## Discussion

The RECUR study is part of the German ministry for Education and Research call for the "establishment of model registers”. The registry will help us identify those patients who will most benefit from specific interventions to prevent recurrences. In addition, the registry’s proposed technical architecture built on federated DICs of different hospitals can be transferred to future registries.

The full digitalization and automation of almost all registry-associated proceedings – from patient inclusion to data acquisition and processing – will effect various limitations. The necessary use of new information technologies such as a smartphone may lead to a preferred selection of young, well-educated and German native-speaking patients. We will estimate the extent of bias by comparing basic characteristics of the study population and the overall group of urolithiasis patients at the participating centres. The increasing use of smartphones across all age and sociodemographic groups will reduce this bias in the future.

A considerable proportion of potential participants may have reservations regarding the automated acquisition, storage and use of their data. We will attempt to address these concerns through a transparent and comprehensive information process. This will include both a comprehensive informed consent form and web-based animated illustrations. In addition, patients will be encouraged to ask the medical staff and their treating physicians at any time if needed.

Retention of patients and adherence to the schedule of questionnaires may be another issue of concern. All participants will be asked to answer questionnaires on a regular basis over a long period. This could be particularly true for participants who have not had any stone-related symptoms for a long time. We established a number of strategies to encourage participants to stick to the project. This includes a pleasing design of the RECUR website and patient app with continuous updates and information relevant to patients with recurrent stone disease. Patients can also opt-in to receive a corresponding RECUR newsletter. We will establish a follow-up mechanism in order to get information on the reasons for patient dropouts. Based on the results, our strategies on patient adherence may be adjusted.

The results of our study may not be fully applicable to all stone patients, as almost all participating centres are highly specialized including 10 of 36 German university hospitals. In future, however, further university and non-university hospitals are to be included in the digital network of the MI-I and the RECUR registry.

Most statistical limitations may be reduced by the expected large sample size. Based on an average number of more than 200 eligible patients per centre per year, we expect a recruitment rate of 500—1000 patients per year. Based on the registry’s technical framework, we believe that a very high number of patients will be recruited in the future by including more hospitals into the nationwide digital network of the MI-I.

We believe that the proposed registry will substantially improve the structural and procedural framework for patients with recurrent urolithiasis. This includes advanced diagnostic algorithms and treatment pathways. The registry will help us identify those patients who will most benefit from specific interventions to prevent recurrences. The RECUR Study protocol and the registry’s technical architecture including full digitalization and automation of almost all registry-associated proceedings can be transferred to future registries.

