## Background

Urinary stone disease (syn. *urolithiasis*) is a widespread disease with tremendous impact on those affected and on societies around the globe. Nevertheless, clinical and health care research in this area seem to lag far behind cardiovascular diseases or cancer. This may be due to the lack of an immediate deadly threat from the disease and therefore less public and professional interest. There is a paucity of data on epidemiology and health care concerning urolithiasis in Germany and around the world. In Germany, Hesse et al. published the only available data on the incidence and prevalence of urinary stone disease in 2003 [1]. According to their data, the incidence and prevalence of urolithiasis are rising (incidence in 1979: 0.54%, 2001: 1.47%; prevalence 2001: 4.77%). This includes recurrent urolithiasis in 50% of patients within 5 years [2].

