### Disease burden and socio-economic impact

The high recurrence rate of urolithiasis is in line with repeated episodes of severe pain and hospitalization. Affected patients may need multiple interventions and operations, including treatment-associated complications. Long-term morbidity includes septicemia, doubled risk of acute or permanent kidney damage, and arterial hypertension after at least one stone-related event, leading to significant limitations in quality of life [3].

In Germany, the numbers of in-hospital treatments for urolithiasis exceed those of any other urological disease including prostate cancer, bladder cancer, and benign prostatic disease [4]. Overall, urolithiasis affects approximately 10% of the population of industrial countries, which corresponds to 8 million patients in Germany [5]. Costs for work days lost and treatment are high exceeding € 500 million and 5.8 million lost working days per year in Germany in 1997 [6]. In the United States, costs of stone disease are projected to exceed $ 4.5 billion annually by 2030 [7].

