### Target population and recruitment

The target population includes all patients with recurrent urinary stone disease (approximately 5% of the population of industrialized countries). The source population comprises all patients with recurrent urinary stone disease (≥ 2 stone-related events) evaluated and treated at participating hospitals of the MIRACUM consortium. Observational units are all patients who give their consent to participate.

Eligible patients will be offered a patient information brochure in participating centres during outpatient or inpatient visits. This brochure informs patients about the purpose of the planned registry. At the same time, the personal benefits of participation will be explained and health professionals in recruiting centres will provide detailed information if necessary. No financial incentives will be provided for participation.

If interested in participation, patients can use a downloadable app to consent and register. To increase adherence, patients can contact the study team in case of upcoming study-related questions or the technical support in case of technical problems.

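### The selection-bias check compares recurrent stone formers with all stone patients, so it mixes participation bias with the effect of the eligibility criterion

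*Protocol article*

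**What the plan says.** Three statements in the protocol article bear on this.

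- **Who can be in the registry.** Target population and recruitment: "The source population comprises all patients with recurrent urinary stone disease (≥ 2 stone-related events) evaluated and treated at participating hospitals". The same section adds: "Observational units are all patients who give their consent to participate". Participants are thus the consenting part of a recurrent-only group, and the target population in that section is recurrent patients too.
- **Which bias is feared.** Discussion: reliance on a smartphone "may lead to a preferred selection of young, well-educated and German native-speaking patients".
- **How it will be measured.** The next sentence of the Discussion says its extent will be estimated by "comparing basic characteristics of the study population and the overall group of urolithiasis patients at the participating centres".

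No other section narrows that comparison group to recurrent or eligible patients.

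**The concern.** The bias named in the Discussion is one of participation: who, among those who could join, actually does. The natural reference is the eligible group. The reference stated is everyone treated for urolithiasis at the centres, whether or not they could have joined. A difference in age or sex between the two groups may then arise because the registry admits only recurrent patients, and not because the app deters some of them.

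This is the only measurement the article states for a limitation that it raises itself. If the comparator is carried unchanged into the analysis plan, readers could be told that selection is present when it is not, or absent when it is present. A larger registry would not help, because the extra term does not shrink with sample size.

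**Working it through.** The article attaches no figure to this check, so there is nothing of its own to reproduce. The structure can be worked out directly.

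**Notation.** For one characteristic, let P be the mean in participants, R in all recurrent (eligible) patients at the centres, F in non-recurrent patients, and r the recurrent share of the overall group. The overall mean is O = rR + (1 − r)F.

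**Decomposition.** P − O = (P − R) + (R − O), and R − O = (1 − r)(R − F). Hence

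P − O = (P − R) + (1 − r)(R − F).

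The first term is participation bias. The second is produced by the entry criterion and vanishes only if R = F or r = 1.

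**Is R = F a safe assumption?** Not on the article's own account. Its Risk factors section introduces male sex among characteristics linked to recurrence (the figures it gives, 5.5% against 4.0%, are prevalences) and lists early onset and family history as risk factors for highly recurrent disease. It gives no size for any difference between recurrent and non-recurrent patients.

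**Value of r.** Recurrent disease is put at "approximately 5% of the population of industrialized countries", and the Disease burden section says "urolithiasis affects approximately 10% of the population of industrial countries". The ratio is 5/10 = 0.5. The Background statement, "This includes recurrent urolithiasis in 50% of patients within 5 years", is a five-year recurrence risk, not a share of hospital patients. The share at these hospitals is not given, so I use 0.3 to 0.7.

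**Spurious part, (1 − r) × d,** where d is the standardised difference between recurrent and non-recurrent patients (assumed 0.2 to 0.4):

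| r | d = 0.2 | d = 0.4 |
|---|---|---|
| 0.3 | 0.7 × 0.2 = 0.14 | 0.7 × 0.4 = 0.28 |
| 0.5 | 0.5 × 0.2 = 0.10 | 0.5 × 0.4 = 0.20 |
| 0.7 | 0.3 × 0.2 = 0.06 | 0.3 × 0.4 = 0.12 |

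**Both directions, using age (all differences assumed).**

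- False signal: recurrent patients 4 years younger, no participation bias. The check shows 0 + (1 − r)(−4) = −2.8, −2.0 and −1.2 years at r = 0.3, 0.5 and 0.7.
- Masking: recurrent patients 4 years older, participants truly 2 years younger than the eligible. The check shows −2 + (1 − r)(4) = +0.8, 0.0 and −0.8 years.

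**After restricting the comparator.** Against all eligible recurrent patients the difference is P − R and the second term is gone. Participants are still part of that group. With participation fraction f and mean N in eligible non-participants, R = fP + (1 − f)N, so P − R = (1 − f)(P − N). The Discussion expects 500 to 1000 recruits a year and more than 200 eligible patients per centre; with eleven sites that is at least 11 × 200 = 2200. So f is at most 500/2200 = 23% to 1000/2200 = 45%, and the contrast would shrink to about 77% to 55% of the difference from non-participants. Comparing with non-participants avoids this.

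**The case against.** **The wording may be shorthand.** This is one sentence in the Discussion of a condensed article, and the article uses the bare disease name elsewhere for its recurrent cohort, for instance when the Objectives ask about the impact of urolithiasis. The authors may have meant the eligible group. That is possible, and the fix is then a correction of wording. But the article says recurrent or eligible where it means so, and this sentence says neither.

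**The comparison may be meant to address generalisability.** The Discussion treats applicability to all stone patients separately and ties it to the specialised nature of the centres. The sentence at issue follows directly on the smartphone concern.

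**The effect may be small.** This stands in part. Contamination arises only for characteristics that differ by recurrence status. The article reports no such difference for education or language, and early onset is not the same as age at the visit. Specialised centres may also see a high share of recurrent patients, which shrinks the term.

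**A corrected comparator would not reach everything.** This also stands. Sociodemographic data come from the app questionnaires, and the clinical data listed under Data set do not include education or native language, two of the three features named.

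A reader might infer that the check cannot measure participation bias at all, or that it would shift the registry's results to a wrong population. The documents support neither. The defect lies in the stated comparator, not in the available data, and it is absent for characteristics unrelated to recurrence. No reweighting from this check is planned, and the article does not feed it into the recurrence or quality-of-life analyses.

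**Conclusion.** The point holds in a limited form. As worded, the check estimates participation bias plus an eligibility effect and cannot tell the two apart for any characteristic that differs between recurrent and non-recurrent patients. Under the assumed ranges (d from 0.2 to 0.4, r from 0.3 to 0.7) the spurious part is about 0.06 to 0.28 standardised units. The true size is unknown, because the article gives neither the recurrent share at its centres nor any difference by recurrence status. Masking or a reversed sign is possible, but is shown here only with assumed age differences. What is affected is the interpretation of a stated limitation; the primary outcome analyses are not. The correction is worth making because it is cheap and this is the only check of the bias that the article describes.

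**What to change.** In the Discussion, and in the analysis plan, define the comparator as patients with at least two stone-related events (the source population already defined under Target population and recruitment) seen at the same centres in the same period. Eligible non-participants are preferable to all eligible patients.

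Obtain the figures through aggregate queries to the data integration centres. State that the check covers only characteristics held in routine data, such as age and sex (assumed here to be in the hospital record), and that education and native language may not be assessable for non-participants.

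The cost is an eligibility filter in a query and a few words in the plan, subject to the local use and access review described under Data Availability. The present check already needs data on patients outside the registry, so no patient contact is added. No weighting analysis is required.

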**Methods:**

RECUR builds on the technical infrastructure of Germany’s Medical Informatics Initiative. Local data integration centres (DIC) of participating medical universities will collect pseudonymized and harmonized data from respective hospital information systems. In addition to their clinical data, participants will provide patient reported outcomes using a mobile patient app. Scientific data exploration includes queries and analysis of federated data from DICs of eleven participating sites. All primary patient data will remain at the participating sites at all times. With comprehensive data from this longitudinal registry, we will be able to describe the disease burden, to determine and validate risk factors, and to evaluate treatments. Implementation and operation of the RECUR registry will be funded by the BMBF for five years. Subsequently, the registry is to be continued by the German Society of Urology without significant costs for study personnel.

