### Sample size calculation

As with many registry studies investigating widespread diseases with high prevalence, sample size is not a major concern. Therefore, we did not perform sample size calculations. We aim at collecting as much and as complete data as possible by reducing a) the effort for including patients into this study and b) the size of the questionnaires to a minimum. Non-responders to the app-integrated questionnaires will automatically receive reminders to increase completeness of data. Considering the high volume of eligible patients at the participating centres, we expect an annual recruitment rate of 500 to 1000 patients.

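### A large sample does not reduce the selection, retention and centre-mix limitations that the Discussion names, and the article states no adjustment of the descriptive estimates for selection into the registry

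*Protocol article*

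**What the plan says.** The Discussion sets out four limitations. Smartphone use may favour younger, better-educated, native German-speaking patients. Some patients may not want their data collected automatically. Participants may stop answering, particularly those long free of symptoms. Almost all centres are highly specialised.

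The next paragraph says "Most statistical limitations may be reduced by the expected large sample size" and supports this with a recruitment forecast: "Based on an average number of more than 200 eligible patients per centre per year", from which 500 to 1000 patients a year are expected. The section Sample size calculation is similar in tone: "sample size is not a major concern", then "Therefore, we did not perform sample size calculations".

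For selection into the registry, the Discussion states "We will estimate the extent of bias by comparing basic characteristics of the study population" with all urolithiasis patients at the participating centres, and expects the bias to lessen as smartphone use spreads. Data analysis assigns descriptive methods to research question 1 (disease burden), with a review of missing-item patterns and unspecified measures to handle them. It plans multiple imputation for question 2 and propensity score methods for question 3.

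**The concern.** A larger sample drawn in the same way reduces random error only. The limitations named are about who enters, who stays and which centres take part, so they are systematic. The Discussion names no limitation of precision that a larger sample would relieve, so the sentence reassures on the wrong count.

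This matters most for question 1, whose purpose is to describe burden: patient-reported outcomes including stone-related quality of life (WISQOL), socio-economic impact and gender differences. If those who enrol differ from those who do not, the descriptive figures are off by an amount that accumulating patients does not remove, while their apparent precision improves. The planned comparison would show part of the problem, but nothing in the article carries its result into the estimates.

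**Working it through.** **Inputs from the article**
- Sites: 11 (Abstract, Methods: "queries and analysis of federated data from DICs of eleven participating sites").
- Eligible patients: more than 200 per centre per year (Discussion).
- Recruitment: "we expect an annual recruitment rate of 500 to 1000 patients" (Sample size calculation).
- Funded period: five years (Abstract, Methods: "Implementation and operation of the RECUR registry will be funded by the BMBF for five years").

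The recruitment range is an expectation. No participation rate is given, so it cannot be re-derived.

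**Step 1: implied participation, f**
- Eligible: 11 × 200 = 2,200 a year as a lower bound.
- f is at most 500/2,200 = 22.7% to 1000/2,200 = 45.5%. With ten sites it is 25% to 50%.
- So at least about 55% to 77% of eligible patients stay outside.

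**Step 2: bias of an unadjusted proportion or mean**

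Bias = (1 − f) × d, where d is the participant minus non-participant difference. The article gives no d; I take 2, 5 and 10 percentage points as assumptions. The number enrolled does not appear in the formula except through f.

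**Step 3: precision and coverage at fixed participation**

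Take a true proportion of 50%, for illustration. Half-width = 1.96 × √(p(1 − p)/n): 4.4 points at n = 500, 3.1 at 1000, 2.0 at 2500 and 1.4 at 5000. Coverage of a nominal 95% interval = Φ(1.96 − b/se) − Φ(−1.96 − b/se), with b the bias and se taken at the biased proportion. Each participation rate is paired with the sample it implies: f = 22.7% gives 500 after one year and 2500 after five; f = 45.5% gives 1000 and 5000.

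| Assumed d | f | Bias | Coverage, year 1 | Coverage, year 5 |
|---|---|---|---|---|
| 2 points | 22.7% | 1.5 points | 89% (n = 500) | 66% (n = 2500) |
| 2 points | 45.5% | 1.1 points | 89% (n = 1000) | 66% (n = 5000) |
| 5 points | 22.7% | 3.9 points | 59% | 3% |
| 5 points | 45.5% | 2.7 points | 59% | 3% |
| 10 points | 22.7% | 7.7 points | 6% | 0% |
| 10 points | 45.5% | 5.5 points | 6–7% | 0% |

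Worked line: d = 5 points, f = 22.7%, n = 2500. b = 0.773 × 0.05 = 0.0386; se = √(0.5386 × 0.4614/2500) = 0.00997; b/se ≈ 3.88; coverage ≈ Φ(−1.92) ≈ 0.03.

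**Step 4: what weighting would do, and its price**

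All values here are assumed. Suppose 70% of participants but 45% of eligible patients are under 50, with an outcome risk of 55% under 50 and 45% above.
- Unweighted: 0.70 × 55 + 0.30 × 45 = 52.0%.
- Eligible group: 0.45 × 55 + 0.55 × 45 = 49.5%.
- Weights: 0.45/0.70 = 0.643 and 0.55/0.30 = 1.833.
- Design effect: 0.70 × 0.643² + 0.30 × 1.833² = 1.298, so the standard error rises by a factor of √1.298 = 1.139, about 14%.

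Weighting removes the full 2.5 points here only because age is the sole driver in the example.

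**The case against.** **The sentence is hedged and limited to statistical limitations.** A reader might infer that the article claims a large sample cures selection bias. It does not say so. The sentence opens a separate paragraph on recruitment, and the four limitations have mitigations of their own: the planned comparison, an information process, engagement measures with follow-up of dropout reasons, and later inclusion of other hospitals. This stands. What remains is that the Discussion names no limitation that sample size would reduce.

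**Some correction is planned.** A reader might infer that the article plans none at all. That is too broad. Multiple imputation for question 2 and the missing-item measures for question 1 bear on the retention limitation. As described, though, they deal with missing data among participants and not with patients who never enrol. The propensity methods balance treatment groups within the registry.

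**A bigger registry need not have worse coverage.** This is correct. If growth comes from higher uptake, the bias falls. Moving from 500 to 1000 a year at d = 5 points takes it from 3.9 to 2.7 points, with coverage 59% in both cases. For a given eligible pool, bias relative to standard error is proportional to (1 − f)√f, which peaks at f = 1/3. Coverage deteriorates when patients accumulate at a fixed participation rate. Adding non-university hospitals may also help, through the centre mix.

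**Weighting is detail for the analysis plan.** The section Machine learning announces a statistical analysis plan, which is not shown and may contain an adjustment. The supportable statement is that none is stated in this article. A later adjustment would not make the Discussion sentence right.

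**The harm is illustrative.** The article mentions no confidence interval for question 1 and gives no participant/non-participant difference. The effect on the associations and treatment contrasts of questions 2 and 3 has not been shown.

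**Conclusion.** The point holds in a limited form. At a fixed participation rate, the selection, retention and centre-mix limitations in the Discussion do not shrink with sample size. By the article's own figures at most about 23% to 45% of eligible patients enrol. For selection into the registry the article states that the bias will be estimated, but not that the question 1 estimates will be adjusted.

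If participants differ from non-participants, the descriptive results stay biased while their precision improves. For assumed differences of 2 to 10 points the bias is 1.1 to 7.7 points, against a half-width that falls from 4.4 points at n = 500 to 1.4 at n = 5000. The direction needs only a non-zero difference; the size rests on the assumed difference, constant participation and an outcome near 50%.

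This is a cheap improvement to a descriptive analysis. It does not show that the registry's results would be wrong.

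**What to change.** 1. **Discussion.** Limit the sentence to random error, and say that selection, retention and centre mix are not reduced by sample size.
2. **Data analysis, research question 1.** Report the descriptive outcomes, including WISQOL, unweighted and, beside them, post-stratified or raked to the eligible recurrent stone patients of the same centres. Use characteristics the centres hold for all patients, for example age, sex and centre.
3. **Discussion, planned comparison.** Restrict the comparison group to recurrent patients. The present comparator is all urolithiasis patients, whereas Target population and recruitment defines the source population by at least two stone-related events.
4. **State what remains.** Weighting corrects only for the characteristics used. Sociodemographic data come from the app (The RECUR patient app), so education and language may be unknown for non-participants, and differences on them may remain uncorrected.

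Cost: one adapted aggregate query per centre and somewhat wider intervals, about 14% in the example above. Aggregated counts suffice, so the rule in Data management and data safety against moving individual patient data between sites is respected.
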